#### Randomization and allocation concealment

This trial will adopt stratified, variable block randomization method with setting a random block size as 2, 4, or 6. An independent researcher, who has no contact with participants, assessors, and acupuncturists, will use SPSS (version 24.0) to generate random numbers with the randomized blocks, dividing 252 participants into two groups at a ratio of 1:1: treatment group and sham group, and randomly allocate them into three different hospitals: Shanghai Municipal Hospital of Traditional Chinese Medicine (TCM), Shanghai Chest Hospital, and Putuo District Central Hospital. The researcher will make random allocation cards, each with its allocated hospital and group recorded, and seal each card into an opaque envelope, which will not be revealed until the first acupuncture treatment.

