#### Primary outcome measure

The primary outcome will be the mean changes in Pittsburgh Sleep Quality Index (PSQI) in week 8 when compared to the baseline. As the most rigorously validated sleep healthy assessment tool, PSQI is a self-rated questionnaire used to assess sleep quality and disturbance over a 1-month time interval. It consists of 24 items to be rated, 19 of which are self-reported and 5 of which are required secondary feedback from a room or bed partner [18]. The seven components are subjective sleep quality, sleep latency, sleep duration, habitual sleep efficacy (SE), sleep disturbance, use of sleeping medication, and daytime dysfunction. The sum of the individual component scores creates one total score (range 0–21). The higher score indicates a worse sleep quality and more severe sleep disorder and vice versa.

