### Statistical methods

#### Sample size estimation

The calculation of sample size is based on the review of acupuncture for insomnia [10]. Referring to this study, the mean difference of PSQI between two groups is assumed to be 2.0 with standard deviation of 4.36 for the both groups. Through PASS system (version 15.0.5) calculating, a sample size of 202 can provide 90% power to reject the null hypothesis with a significance level of 0.05 using a two-side two-sample T-tests assuming equal variance. Considering the expected dropout rate of 20%, the final sample size is 252, 126 for each group.

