#### Statistical analysis

A full analysis set (FAS) is based on ITT principle that is including all the qualified participants who meet the inclusion criteria, who receive the intervention at least once, and who provide outcome assessment at least once. In statistical analysis, any the missing primary outcome will be replaced by the data from last time point according to ITT principle. A Per-Protocol Set (PPS) will be used to analyze those who completed the trial without a major violation of the protocol [23]. A Safety Analysis Set (SAS) is based on the principle of exposure to observe safety indicators for any participants received the intervention at least once.

All analysis will be performed in SPSS24.0. Continuous data will be represented by average, standard deviation, median, minimum value, and maximum value through *t* test; rank-sum test is used for ranked data, while chi-square test is adopted to analyze categorical data [24]. (1) Statistical description: Continuous data from week 0 to week 20 will be presented as MD ± SD. *t* test will be used to compare the difference from baseline in both groups and compare variations after intervention between two groups. (2) Equilibrium analysis: To measure the equilibrium at baseline, *t* test or chi-square test is used to compare demographic data and other basic data at baseline, including name, age, marital status, occupation, education, course of disease, pathologic typing of lung cancer, previous treatment of lung cancer, smoking, drinking, tea, coffee, exercise, pain level, other diseases, ECOG score, PSQI score, data from actigraphy, QLQ-C30 score, PHQ-9 score, and dose of hypnotics. Frequency (composition ratio) will be adopted to describe categorical data of two groups at all time points. (3) Safety analysis: all occurred adverse events will be recorded in both groups. Numbers or the incidence rate in the two groups will be analyzed by chi-square test.

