## Abbreviations

EA: Electro-acupuncture
CRI: Cancer-related insomnia
PSQI: Pittsburgh Sleep Quality Index
QLQ-C30: Quality of Life Questionnaire Core-30
PHQ-9: Patient Health Questionnaire-9
TESS: Treatment Emergent Symptom Scale
CBT: Cognitive Behavioral Therapy
TCM: Traditional Chinese Medicine
CONSORT: Consolidated Standards of Reporting Trials
STRICTA: Standards for Reporting Intervention in Controlled Trials of Acupuncture
DSM-V: The Diagnostic and Statistical Manual of Mental Disorders, Fifth Edition
APA: American Psychiatric Association
ECOG: Eastern Cooperation Oncology Group
DSMB: Data Safety Monitoring Board
SE: Sleep efficacy
EORTC: European Organization for Research and Treatment of Cancer
DSM-IV: Diagnostic and Statistical Manual of Mental Disorders
CRF: Case report forms
AEs: Adverse events
SAE: Severe adverse event
FAS: Full analysis set
ITT: Intention-to-treat principle
PPS: Per-Protocol Set
SAS: Safety Analysis Set
ANCOVA: Analysis of covariance

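### The primary comparison is an unadjusted t test on PSQI change; ANCOVA on week-0 PSQI and the stratification factor would be at least as precise at no cost, and the SD of 4.36 needs defining

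*Protocol article*

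**What the plan says.** Under Primary outcome measure the endpoint is fixed: "The primary outcome will be the mean changes in Pittsburgh Sleep Quality Index (PSQI) in week 8 when compared to the baseline". Under Statistical analysis, in the item on statistical description, a t test "test will be used to compare the difference from baseline in both groups and compare variations after intervention between two groups". The Abstract also lists t, rank-sum and chi-square tests. No model with baseline PSQI or a stratum term is described. ANCOVA appears only in the list of abbreviations ("ANCOVA: Analysis of covariance").

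Under Randomization and allocation concealment: "This trial will adopt stratified, variable block randomization method with setting a random block size as 2, 4, or 6". The stratification factor is not named. The three hospitals are mentioned in the next sentence, and each allocation card carries its hospital, so hospital is the natural reading.

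Under Sample size estimation: "the mean difference of PSQI between two groups is assumed to be 2.0 with standard deviation of 4.36 for the both groups"; "a sample size of 202 can provide 90% power to reject the null hypothesis with a significance level of 0.05"; and, once the section has named a two-sided t test with a common SD as the sizing method, "Considering the expected dropout rate of 20%, the final sample size is 252, 126 for each group". The section does not say whether 4.36 is the SD of a PSQI score or of its change. It gives no baseline to week-8 correlation.

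**The concern.** This is a stated method, not a detail left to a later document: the endpoint, the test and the sample size all point to an unadjusted two-sample comparison of change. The trial schedules PSQI at week 0 and stratifies the randomisation, but the analysis uses week-0 PSQI only by subtracting it and does not use the stratum at all.

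Subtraction fixes the weight on baseline at 1, whereas ANCOVA estimates the weight from the data. When the correlation is low, subtraction adds noise. What is at stake is precision and the security of the 90% power, not bias: in a randomised trial both analyses estimate the same treatment effect. The undefined SD adds to this, because the power of a test on change rests on the SD of change.

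**Working it through.** **Inputs from the protocol article.** Difference 2.0; SD 4.36 in both groups; two-sided alpha 0.05; 202 evaluable, so 101 per arm; 20% dropout; entry PSQI above 11; PSQI range 0 to 21.

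**Assumptions, not in the article.** Correlation r from 0.2 to 0.7, and baseline SD (sB) of 2 to 3. The range for sB follows from the entry rule: eligible screening scores are 12 to 21, a uniform spread over those ten values has SD 2.87, and the largest SD possible on that range is (21 − 12)/2 = 4.5.

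**1. The plan's own figure.** The noncentrality is 2.0 / (4.36 × √(2/101)) with 200 df, and the noncentral t gives power 0.9005. With 100 per arm it is 0.8976, so 101 per arm (202) is the smallest size that reaches 90%. Dropout: 202 / 0.8 = 252.5, against the stated 252. The figures reproduce.

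**2. Formulas.** With sW the week-8 score SD:
- SD of change = √(sB² + sW² − 2·r·sB·sW)
- ANCOVA residual SD = sW·√(1 − r²)
- Difference of the two variances = (sB − r·sW)², which is never negative. ANCOVA is therefore never less precise, except for a few degrees of freedom out of 200, and the gain is zero when r = sB/sW.

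**3. If 4.36 is the week-8 score SD** (sW = 4.36, 101 per arm, sB from 2 to 3):

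| r | SD of change | t test power | ANCOVA SD | ANCOVA power |
|---|---|---|---|---|
| 0.2 | 4.42-4.77 | 84.2-89.3% | 4.27 | 91.2% |
| 0.3 | 4.22-4.49 | 88.3-91.8% | 4.16 | 92.5% |
| 0.4 | 4.00-4.19 | 92.2-94.2% | 4.00 | 94.3% |
| 0.5 | 3.78-3.86 | 95.5-96.3% | 3.78 | 96.3% |
| 0.7 | 3.11-3.29 | 99.0-99.5% | 3.11 | 99.5% |

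The t test reaches 90% once the SD of change is no more than 4.36, that is once r ≥ sB/(2 × 4.36): 0.23 for sB = 2 and 0.34 for sB = 3.

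**4. If 4.36 is the SD of change.** The t test has 90% at any r. Solving the first formula for sW gives sW = r·sB + √(4.36² − sB²(1 − r²)), and the ANCOVA SD follows:

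| r | ANCOVA power, sB = 2 | sB = 2.5 | sB = 3 |
|---|---|---|---|
| 0.2 | 92% | 94% | 97% |
| 0.3 | 91% | 92% | 94% |
| 0.5 | 90% | 90% | 90% |
| 0.7 | 95% | 93% | 92% |

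**5. Omitted stratum.** Suppose strata are hospitals, allocation is balanced within them, the within-hospital SD of change is 4.36 (variance 19.01), and hospital mean changes have SD h. The t test's pooled variance then contains h², while the true variance of the arm difference does not. The standard error is too large by √((19.01 + h²)/19.01):
- h = 1: factor √(20.01/19.01) = 1.026; the true type I error is P(|Z| > 1.96 × 1.026), about 4.4%.
- h = 2: factor √(23.01/19.01) = 1.100; about 3.1%.

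Constant differences between hospitals in PSQI level cancel in a change score, so only differences in mean change count.

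**The case against.** The strongest defence is that an unadjusted t test on change is valid, matches the method used for sizing, and that covariates are often left to an analysis plan, which is not shown. The first two parts stand. The third does not remove the point, because the article states a method and an adjusted primary analysis would have to depart from it. The abbreviation entry hints at an ANCOVA but specifies nothing.

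Four stronger readings are tempting, and the document does not support them.

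- *Baseline PSQI is ignored.* It is not: a change score subtracts it. It is only not used as a covariate.
- *The trial is underpowered.* With equal SDs of 4.36 at baseline and week 8, the SD of change at r = 0.3 is 4.36 × √(2 × 0.7) = 5.16, and power is 78%. But a baseline SD of 4.36 is close to the 4.5 maximum for scores of 12 to 21, so almost everyone would have to sit at one end or the other. Week-0 scores may drift a little from screening, but not that far. And if 4.36 is the SD of change, the 90% does not depend on r at all.
- *Leaving out the stratum invalidates the test.* The error is conservative, not a bias. It is small unless mean change differs between hospitals by amounts comparable to the assumed treatment effect of 2.0, for which the document gives no evidence.
- *Within-arm tests are offered as proof of efficacy.* They sit under statistical description, and the stated objective is a comparison with sham EA. Both arms may improve through regression to the mean after selection on a high PSQI, so a caution is reasonable, but no misuse is planned.

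**Conclusion.** The point holds as a matter of efficiency and clarity, and should be acted on. The planned primary test is valid and the stated 202 and 252 are arithmetically right, but a stated method can be replaced at no cost by one that is at least as precise.

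The gain is modest. Under the assumed baseline SD of 2 to 3, it runs from about 2 to 7 percentage points of power at r = 0.2 to almost nothing at r = 0.5 or above if 4.36 is a week-8 score SD. It runs from about 0 to 7 points if 4.36 is the SD of change. ANCOVA keeps at least 90% in every case examined; the t test falls below it only under the score reading with a low correlation. The baseline SD and r are my assumptions, and the document cannot settle which SD was meant. A material effect of omitting the stratum would need large differences in mean change between hospitals.

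**What to change.** - Make the primary analysis an ANCOVA of week-8 PSQI on arm, week-0 PSQI and the stratification factor, naming that factor (hospital, if that is what was meant). Report the adjusted difference with its 95% CI.
- Use the same form for actigraphy, QLQ-C30 and PHQ-9.
- State whether 4.36 is the SD of the PSQI score or of its change and, if of the score, the baseline SD and correlation assumed.
- Say that within-arm comparisons with baseline are descriptive only.

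The cost is wording in the protocol and analysis plan. Table 1 already schedules PSQI, actigraphy, QLQ-C30 and PHQ-9 at week 0, and hospital is recorded on the allocation card. The sample size need not change on this account.

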### Quality control

There may exist some potential protocol deviation in this trial. Firstly, it is a multicenter trial, so it demands more than one acupuncturist and assessors, which may cause treatment bias due to different understanding of blinding method and acupuncture methods from different researchers. Secondly, patients may not be in compliance with the intervention time or assessment time or receive any contraindicate treatment as the protocol stated. Thirdly, due to the different conditions of amounts of lung cancer patients, different hospitals may recruit eligible patients with varying speed, which will also lead to protocol deviation. To address the potential bias and guarantee the quality of this trial, despite of improving patients’ compliance, researchers should also strictly follow the protocol and perform adequate randomization, successful blinding, and concealment. As licensed doctors, all acupuncturists and assessors from three hospitals will be required to receive standard training prior to the beginning of the trial. The training program includes recruitment, interventions, and detailed assessment process. Most of all, they will be trained not to discuss the treatment procedure with the patients. Besides, meetings will be held periodically to monitor progress, and researchers will communicate with each other about the arisen problems during the trial and the best solutions. In addition, an independent Data and Safety Monitoring Board (DSMB) will be established to supervise whether the study design meets the standard guideline, and guarantee the preciseness of this trial. The committee consist of five members in different fields: [name] in acupuncture from Virginia University of Integrative Medicine, [name] in psychology from Shanghai Mental Health Center, [name] in statistics from Yueyang Hospital of Integrated Traditional Chinese and Western Medicine, and [name] and [name] in oncology from Shanghai Pulmonary Hospital, who all have to declare no conflict of interest in this study. DSMB is responsible for monitoring data, identifying problems, examining collected data, and controlling bias. Once they find there existing any problems or adverse events during the trial, they have the right to suspend the trial until the problem has been solved or even terminate it at any point.

## Discussion

Nowadays, acupuncture therapy has been widely used in clinical practice as a popular non-pharmacological alternative treatment for insomnia, as more and more research has shown its efficacy and safety. However, most studies focus on acupuncture for general insomnia and there are fewer high-quality studies about acupuncture on treating CRI among lung cancer patients. Thus, it is expected that this study will contribute to adding more strong evidence for the effectiveness of acupuncture for CRI.

The main purpose of this trial is to present a well-designed multicenter randomized single-blinded sham-controlled trial to evaluate the efficacy and safety of electro-acupuncture for insomnia in patients with lung cancer. However, previous researches related to CRI have some limitations, including inexact inclusion criteria, substandard study design, unpractical methods, and indefinite factors decreasing quality of insomnia among lung cancer patients. So we have made some improvements in this trial. Firstly, we design this trial with two groups, EA and sham EA, to identify whether it is real electro-acupuncture that plays a role in treating insomnia in lung cancer patients or it is just the placebo effect. We will limit the inclusion criteria to specific cancer type, ongoing cancer therapy, and tailor points selection for each patient. Secondly, given participants’ psychological condition, oral intake of hypnotics is allowed to alleviate their insomnia symptoms and ensure that each participant gains the optimum benefit from this trial. Thirdly, we will apply semi-standard point selection, composed of core acupoints and additional acupoints, with reference of acupuncture literature and the acupuncturists’ clinical experiences. From additional acupoints, only four of them will be chosen according to specific symptoms of participants, strictly following standardization of syndrome differentiation and treatment administration of TCM. All acupoints will be located with reference to the International Standard Library of Chinese Medicine [25]. Finally, this trial will apply both objective and subjective outcomes representing sleep quality and the related symptoms among lung cancer patients. Most of the acupuncture studies on insomnia have used only patient-reported outcomes; furthermore, a small number of studies using objective outcomes such as actigraphy to show consistent results on the effects of acupuncture [23]. We intend to compare the difference between objective and subjective outcomes and unearth more thought-provoking questions based on the outcomes in this trial.

Although this trial is designed to address the limitations in previous trials, there still remain potential challenges waiting for us to solve. Firstly, to ensure the successful implementation of protocol, acupuncturists will accept training before the beginning of the trial and prepare to reasonably dispose of patients through systematically studying and mastering detailed protocol, particularly in terms of the manipulation of EA and sham acupuncture device and measurement questionnaires. Secondly, to achieve adequate participant enrollment to target sample size in time, the patients will be recruited from three hospitals in Shanghai: Shanghai Municipal Hospital of Traditional Chinese Medicine (TCM), Shanghai Chest Hospital, and Putuo District Central Hospital, which are all comprehensive hospitals with numbers of lung cancer patients on a daily basis. Oncologists in these hospitals have joint this trial, and they will be responsible to introduce this research to eligible patients and recruit them. We also have made some leaflet, billboard inside hospitals, and recruitment link on the Internet to attract patients’ attention. Thirdly, to ensure compliance from patients and ensure minimal loss to follow-up, we will use the following strategies. Clinical trial publicity brochures will be handed out to all hospitals to popularize clinical trial knowledge. Before assigning informed consent, detailed attentions should be explained to participants, including trial protocol and intervention demands, positive effects, and potential adverse events. After fully consideration, they can assign the informed consents. Besides, we will strengthen the public education of medical knowledge to patients, care for the patients, and improve their quality of life in all relevant aspects. For instance, we will make reasonable arrangements for treatment time and consultation time by phone or e-mail to increase their attendance rate. Besides, free acupuncture treatment will be promised by acupuncturists if the patients are not satisfied with the results of their treatment during the trial [26]. And participants will get adequate transportation allowance if they have completed all the treatment and follow-up. What is more, more flexible methods will be adopted to measure patients during the follow-up period, like calling to ask the questions or making an electronic edition of PSQI through message or other communication software. We have successful recruiting experience in our previous studies related to insomnia whose dropout rates were all low. Therefore, we are confident that we will have low dropout rate in this trial.

It still remains uncertain that how EA improve sleep condition in insomnia patients. However, plenty of studies have already demonstrated the potential physiological mechanism through which EA could provide benefit in insomnia. A review [27] make a comprehensive summary of how acupuncture improves sleep quality through regulating monoamine neural transmitters, inhibitory neurotransmitter, cytokines, and immediate-early gene, which plays a vital role in high-quality sleep. A laboratory trial found EA stimulation can induce the increasing concentration of *β*-endorphin, which might be beneficial of sleep by conducting a rat experiment [28]. Acupuncture can also give a dual-directional balancing regulation of autonomic nervous system, sympathetic nervous and parasympathetic nervous included, which might have a sleep-promoting effect [29]. Although this trial is not designed to run any laboratory tests, the results can also provide sufficient evidence to lay a valid foundation on further experimental researches in laboratory, in which the exact mechanism of acupuncture affecting sleep may be found.

To sum up, in this trial, we will standardize point selection, manipulation, assessment, and therapists’ clinical experience following the CONSORT statement and STRICTA recommendations rigorously. We expect this study will confirm the efficacy and safety of acupuncture on insomnia in patients with lung cancer, contributing to filling the gap of the CRI field and providing a promising curative intervention for lung cancer survivors with insomnia in clinic.

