**Method:**

This is a protocol for a multicenter randomized single-blinded sham-controlled trial. We will randomly assign 252 eligible patients with lung cancer-related insomnia into two groups at a ratio of 1:1, the treatment group (EA) and the control group (sham EA). All treatment will be given 3 times per week for 8 weeks, and a 12-week follow-up will be conducted. The primary outcome will be measured by the Pittsburgh Sleep Quality Index (PSQI). The secondary outcomes will include sleep parameters recorded from the actigraphy, scores from Quality of Life Questionnaire Core-30 (QLQ-C30), and Patient Health Questionnaire-9 (PHQ-9). All adverse effects during the trial will be assessed by the Treatment Emergent Symptom Scale (TESS). All analyses will be based on ITT principle and performed with the statistical software SPSS (version 24.0) by *t* test, rank-sum test, chi-square, and so on. A two-sided significance level will be set at 5%.

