#### Blinding

This is a single-blinded (patient-assessor-blinded) study. Before treatment, all participants will be informed that they will be assigned to either EA group or sham EA group. They will also be required to wear eye-patch in a private quiet space during the whole treatment period. The principal researcher, assistant researchers, data analysts, assessors, and statisticians will all be blinded to the group allocation. Only the acupuncturist will know their allocated groups, but they will not be informed of any qualitative information on the patient, including severity of lung cancer-related insomnia, merger disease, or dose of hypnotics. This trial will set up a data safety monitoring committee according to the guidance of Data Safety Monitoring Board (DSMB). Experts in the committee will be responsible for monitoring the data safety and have the right to reveal blinded data.

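### Free acupuncture is promised to dissatisfied patients with no stated start date, so real acupuncture could reach the sham arm before the week-12 and week-20 assessments

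*Protocol article*

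**What the plan says.** The promise stands in the Discussion of the protocol article, in a list introduced by "to ensure compliance from patients and ensure minimal loss to follow-up, we will use the following strategies". The item reads: "free acupuncture treatment will be promised by acupuncturists if the patients are not satisfied with the results of their treatment during the trial". It gives no delivery date, no PSQI threshold and no restriction to one arm. The next item in the list is a transport allowance that depends only on completing treatment and follow-up.

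Other sections bear on it:

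- **Primary outcome measure:** "The primary outcome will be the mean changes in Pittsburgh Sleep Quality Index (PSQI) in week 8 when compared to the baseline". The instrument is self-rated: "PSQI is a self-rated questionnaire used to assess sleep quality and disturbance over a 1-month time interval".
- **Abstract, Method:** "All treatment will be given 3 times per week for 8 weeks, and a 12-week follow-up will be conducted". Table 1 schedules PSQI and hypnotic dose at weeks 12 and 20 as well as week 8.
- **Statistical analysis:** "Continuous data from week 0 to week 20 will be presented as MD ± SD", so the follow-up data are part of the planned results.
- **Blinding:** "Only the acupuncturist will know their allocated groups". These are the staff who are to make the promise.
- **Quality control:** on the training of acupuncturists and assessors, "they will be trained not to discuss the treatment procedure with the patients".

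**The concern.** The promise combines three features that sit badly together.

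1. The benefit depends on the patient's own unfavourable view of the result. That is close in kind to what a self-rated sleep questionnaire captures, so it gives a patient some motive to describe the result as poor.
2. The offer is made by the only people who know the allocation, so it could be made or stressed differently in the two arms.
3. Its delivery is not tied to the end of data collection. The benefit is itself acupuncture, so giving it during follow-up would expose some sham patients to the treatment under test.

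The third feature is the most direct risk. If electro-acupuncture (EA) works, dissatisfaction and therefore take-up would tend to be greater in the sham arm. The week-12 and week-20 contrasts, which show whether any benefit lasts, would then shrink for a reason unrelated to durability. As the article describes the trial, such sessions need leave no trace: Table 1 schedules the recording of hypnotics but has no row for acupuncture received outside the trial.

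**Working it through.** **1. The plan's own figure.** Inputs from Sample size estimation: difference 2.0, SD 4.36, two-sided 5% level, 90% power, two-sample t test.

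- Standard error with 101 per arm: 4.36 × √(2/101) = 0.614.
- Noncentrality: 2.0 / 0.614 = 3.26, with 200 degrees of freedom. Power is 0.9005, so the 202 evaluable patients reproduce.
- Dropout: 202 / 0.8 = 252.5, against 252 stated.

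Nothing in the sample size is wrong. It only supplies the scale for what follows.

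**2. Which data could be reached.** Set Table 1 against a treatment period that ends at week 8:

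| Measure | Week 8 | Week 12 | Week 20 |
|---|---|---|---|
| PSQI | yes | yes | yes |
| Hypnotic dose | yes | yes | yes |
| Actigraphy, QLQ-C30, PHQ-9 | yes | no | no |

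Free sessions given after week 8 could alter only PSQI and hypnotic dose at weeks 12 and 20. With a one-month recall, the week-12 PSQI covers roughly weeks 8 to 12 and the week-20 PSQI roughly weeks 16 to 20, so both windows lie inside the exposed period.

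**3. Size of the dilution, under assumptions.** The documents give no take-up rate. Let f be the fraction of the sham arm that receives real acupuncture in time to affect the assessment. Assume that these patients gain the full effect, that the EA arm gains nothing further, and that the undiluted follow-up difference is 2.0. Then the expected difference is D = 2.0 × (1 − f).

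| f | D (points) | Power at D, 101 per arm, SD 4.36 |
|---|---|---|
| 0 | 2.0 | 0.900 |
| 10% | 1.8 | 0.831 |
| 20% | 1.6 | 0.737 |
| 30% | 1.4 | 0.622 |
| 40% | 1.2 | 0.495 |
| 50% | 1.0 | 0.368 |

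The power column is a yardstick only, because the article claims no power for weeks 12 or 20. A partial effect, or take-up that also benefits the EA arm, would make the dilution smaller.

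**4. Week 8.** Let the promise shift reported PSQI by s(sham) and s(EA). The expected contrast, sham minus EA, is the true difference plus s(sham) − s(EA). Equal shifts cancel and the contrast is unbiased. A bias appears only if the two shifts differ.

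**The case against.** The strongest defence has four parts.

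**The trigger is not a score.** No PSQI answer earns or forfeits the benefit. Blinded assessors collect the data, and the acupuncturists who make the promise are not told how severe the insomnia is. This stands. A reader might infer that the plan rewards bad scores on its primary outcome, but the text ties the promise to dissatisfaction and nothing more. A motive to report poorly is a fair inference, not a stated rule.

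**Both arms get the same promise, and patients are blinded.** This also stands. A reader might infer an inflated false-positive rate at week 8. Under no true effect, an assumed excess of 0.25, 0.5 or 1.0 points in sham reporting would raise the two-sided rejection rate from 5% to about 7%, 13% or 37%. The documents support none of these shifts. With no true effect, EA cannot be what makes sham patients less satisfied, so the excess would have to come from something such as patients guessing their allocation. If EA does work, worse sham scores are first of all the treatment effect itself. A shift in the other direction would lower power instead.

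**The timing is open, not wrong.** The closing words of the promise most naturally describe the treatment already received, so delivery after follow-up is an equally available reading, and no crossover is planned. This stands too. But the same words allow delivery during follow-up, and this is a rule the article chose to state, with a benefit, a trigger and a messenger. It is not a detail simply left to a fuller document.

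**No conflict with the staff training.** The training bars discussion of the procedure, and a promise of later care need not reveal procedure or allocation. That is fair, and the point does not rest on a contradiction. What remains is that unblinded staff make an offer about results.

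**Conclusion.** The concern holds in limited form. As written, the promise is tied to a self-judged poor result, is made by unblinded staff and is not deferred past week 20. It therefore permits real acupuncture in the sham arm while PSQI and hypnotic dose are still being collected. If that happened, with take-up concentrated in the sham arm, the week-12 and week-20 contrasts would be diluted. For PSQI, a 2.0-point difference would fall to between 1.8 and 1.0 at assumed take-up of 10% to 50% with full effect. Those rates are illustrations, not estimates.

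The week-8 primary endpoint is unaffected by crossover after week 8. Bias there through reporting is possible but needs an unequal response between arms, which the documents neither show nor exclude. The point is worth correcting before enrolment, but it does not undermine the primary analysis.

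**What to change.** Replace the sentence in the Discussion, and align the consent information, so that:

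- the retention benefit does not depend on satisfaction or results: either the same offer to every participant, or reliance on the existing transport allowance for completion;
- any free acupuncture offered as that benefit can be redeemed only after the week-20 assessment;
- the offer is described in identical terms to everyone in the consent information, not made by the acupuncturists;
- any non-trial acupuncture up to week 20 is recorded on the case report form.

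The cost is a sentence or two in the protocol and consent form and one extra recorded item. There may be some additional free sessions after week 20 if the offer is extended to all, and the retention incentive may be slightly weaker. The Trial status section describes the trial as still in preparation, so the change can be made before any patient has been given the promise.
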